**Description**

Obesity is known as one of the civilization diseases and it is a serious problem of the 21^st^ century in both developing and developed countries and the percentage of people struggling with overweight shows an upward tendency. From the viewpoint of science, obesity is considered as chronic, low-grade inflammation of the body and it negatively affects its function, which often leads to more serious lesions. In recent years, studies have shown that adipose tissue apart from controlling energy homeostasis of the body also performs endocrine functions. The negative effects of obesity comprise insulin resistance, the development of diabetes mellitus type 2, cardio-vascular diseases, hypertension, atherosclerosis. In recent years, studies have shown that adipose tissue apart from controlling energy homeostasis of the body also performs endocrine functions. Adipose cells – adipocytes secrete biologically active substances - adipokines, which operate within adipose tissue, as well as further organs and tissues. In the excess adipose tissue we can observe hyperplasia of the volume of adipocytes, which causes impaired secretion of adipokines disrupted lipid homeostasis, increased susceptibility to metabolic and cardiovascular diseases and reversible changes in the cells of the immune. In addition, excess adipose tissue, reduces the bioavailability of vitamin D3.

Increasingly, cryostimulation could be used as a method of prevention and treatment of obesity. The anti-inflammatory effects of cryotherapy can alter endocrine properties of adipose tissue, because controlled hypothermia may act therapeutically by inducing physiological and biochemical changes of the body. Due to the innovative nature of the research and its specifics, available sources on the subject of whole body cryostimulation for obese people are limited and do not provide unambiguous results, because of the different number of sessions, duration of cryostimulation and the differentiation between the examined groups. So it is important to explore and continue further studies in order to use this knowledge in the struggle with obesity in adults.

In obesity, lipid profile is disturbed but cold-induced thermoregulation, increases the use of lipids, thus whole body cryostimulation has a positive effect on the lipid profile. The association between adipose tissue and vitamin D in obese is still debated by scientists. The role of vitamin D in connection with adipokines and cryogenic temperatures is still unclear, therefore these studies can provide vital new information.

The endocrine role of adipose tissue in obesity and accompanying metabolic disorders is complex and far from being fully explained, so the results obtained will allow for a broader perspective of the problem of obesity and improve preventive and therapeutic possibilities of fighting with its negative of effects. There is no doubt that the obtained results can provide valuable information for adipokines, which have not been studied yet in relation with whole body cryostimulation. The planned research will expand our knowledge of the link between selected adipokines, cytokines, lipid profile, indicators of morphological and concentration of 25(OH)D and it will help us understand the relations between specific adipocytokines, it will facilitate their use as markers of disorders associated with obesity, and thus it will enable sufficiently early prophylaxis.

**Research Project** **objective**

The aim of the proposed research will be the evaluation the effect of 20 whole body cryostimulation treatments on endocrine activity of adipose tissue, and thus the effect on the level of selected adipocytokines, reduction of inflammation in people with excessive adipose tissue and improve lipid metabolism.

**Research Methodology**

30 men aged 20-25 will be qualified to participate in the research. The control group will be consist of men with normal adipose tissue (15 people) and the experimental group will be made up of subjects with a higher percentage of body fat (> 25%). All participants will be subjected to whole body cryostimulation. Participation in the research project will be voluntary, and the absolute condition for participation will be written consent and no contraindications to systemic cryostimulation and and no medical contraindications.

Research inclusion criteria: age 20-25, males, no contraindications to whole body cryostimulation, medical qualification, normal (<23%) or increased (>25%) percentage of adipose tissue determined for age and sex.

Research exclusion criteria: cancer, advanced cardio-respiratory diseases, cardiac arrhythmias, previous blocked arteries, hypertension (>160/100 mmHg), transient ischaemic attacks, improper operation of the thyroid, diabetes, cold intolerance, frostbite, skin damage, kidney, liver or bladder disease, stroke, claustrophobia, smoking, total cholesterol (>300 mg/dL), weight-reducing diet, taking anti-inflammatory drugs.

Before commencement of the research, medical history and medical examination will be carried out in all participants, in order to exclude metabolic disorders and contraindications for whole body cryostimulation. The nutritional dietary will be interviewed and obtained data will be analyzed using the program Diet 5.0. Participants will be asked not to change their nutritional habits and not to take any physical activity during the whole experiment. Also they will be informed about the purpose of the research, methodology, possible sides effects and the possibility of cancellation of participation at every stage of the experiment.

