**Whole body cryostimulation**

All participants in the experiment will be subjected to 20 sessions of whole body cryostimulation (1 treatment per day, from Monday to Friday, except on holidays) at -120^O^C for 2-3 minutes in the Malopolska Cryotherapy Centre in Krakow. Every entrance to the chamber will be preceded by a 30-second period of adaptation in the porch at -60°C. Before entering the chamber, subjects will have to remove glasses, contact lenses, jewellery and precisely dry the skin, in order to eliminate the feeling of cold during cryostimulation. A suitable outfit during cryotherapy will be: shorts, socks to mid-knee, wooden clogs, gloves and ear- and headgear. The nose and mouth will be covered with a surgical mask. At the same time, in the cryogenic chamber, 4 people will be able to stay, moving slowly, one after the other, breath slowly (short breath, long exhalation). During cryostimulation it is forbidden to talk, contact or make additional movements. Contact with the study group will be maintained by the camera and voice system. They will be instructed to leave the chamber if they feel badly or after hearing the signal that indicates the end of the treatment. Before each treatment systolic and diastolic blood pressure will be checked in order to eliminate contraindications and subjects will be informed to report every time ailments before cryostimulation.

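### Both the 'control' and the 'experimental' group receive all 20 cryostimulation sessions, so no comparison in the design isolates the treatment effect named in the objective

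*Protocol*

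**What the plan says.** The Research Project objective section gives the aim as "evaluation the effect of 20 whole body cryostimulation treatments on endocrine activity of adipose tissue", and through that on adipocytokine levels, inflammation and lipid metabolism.

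Research Methodology plans a total of 30 men in two groups. One of them is introduced in these words: "The control group will be consist of men with normal adipose tissue (15 people". The other, labelled experimental, has body fat above 25%. The inclusion criteria give the dividing line as "normal (<23%) or increased (>25%) percentage of adipose tissue determined for age and sex". On treatment, the same section says "All participants will be subjected to whole body cryostimulation". The section on whole body cryostimulation repeats this with the number of sessions: "All participants in the experiment will be subjected to 20 sessions of whole body cryostimulation".

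Research Methodology also gives one instruction to everybody: "Participants will be asked not to change their nutritional habits and not to take any physical activity during the whole experiment".

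The Blood collection section lists four fasting morning draws: one before treatment, one after session 10, one after session 20, and one a week after the end. The outcomes listed under Marking indicators of blood include 25(OH)D, lipids, adipokines and inflammatory cytokines.

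**The concern.** The objective asks what the treatment does. Answering that needs some estimate of what would have happened over the same weeks without it. The group called control does not supply one, because it is treated in full. It is a reference for adiposity, not for treatment.

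Two conclusions are at risk. A change over time may be read as an effect of cryostimulation when part or all of it is background change. A difference between the groups, or the lack of one, may be read as treatment against control when both were treated. The labels 'control' and 'experimental' invite the second reading.

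Background change is a practical matter here. For men who were active beforehand, the request to take no physical activity is a second change that coincides with treatment, and it may move lipids and inflammatory markers. 25(OH)D can vary with season. With a single pre-treatment sample, no background trend can be estimated from the data.

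**Working it through.** **Reproduction.** The protocol gives no significance level, power, effect size or SD, so there is no stated figure to reproduce. The check is whether any contrast in the design identifies the treatment effect.

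**Inputs from the protocol.** 30 men in total, 15 of them in the control group, so 30 − 15 = 15 in the experimental group. All have 20 sessions, one per weekday: 20 / 5 = 4 weeks, or about 5 weeks to the last draw, longer if holidays intervene. There is one draw before treatment and three from session 10 onwards.

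**What each contrast estimates.** Let E_H and E_N be the effects of cryostimulation in the high-fat and normal-fat men. Let T_H and T_N be the changes each group would have shown over the same weeks without it.

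| Contrast | What it estimates |
|---|---|
| Change within high-fat men | E_H + T_H |
| Change within normal-fat men | E_N + T_N |
| Difference in change, high-fat minus normal-fat | (E_H − E_N) + (T_H − T_N) |

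None of these equals E_H or E_N. The first two do so only if T is zero. The third never does unless E_N happens to be zero and the background changes are equal. Because the groups are not randomised, T_H = T_N cannot be assumed either: previous activity, for example, may differ between lean and high-fat men.

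**Within-group illustration.** Assumptions, none from the protocol: two-sided 5% paired t-test, no treatment effect at all, and a background drift of d SDs of the change score. The test statistic is noncentral t with 14 degrees of freedom and noncentrality d × √15; the critical value is 2.145.

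| Assumed drift d | Noncentrality d × √15 | Probability of a significant result |
|---|---|---|
| 0 | 0 | 5% |
| 0.2 | 0.775 | 11% |
| 0.3 | 1.162 | 19% |
| 0.5 | 1.936 | 44% |
| 0.75 | 2.905 | 77% |

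Pooling all 30 men makes this worse, not better. At drifts of 0.2, 0.3, 0.5 and 0.75 SD the probabilities are about 19%, 36%, 75% and 98%.

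**Between-group illustration.** Assume a true effect of 0.8 SD in both groups and the same background change. Then (E_H − E_N) + (T_H − T_N) = (0.8 − 0.8) + 0 = 0. In 40,000 simulated trials of 15 against 15, the two-sample t-test was significant in 4.9%, which is just the nominal error rate. A real and equally strong effect in both groups is invisible to the comparison with the control group.

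**The case against.** The strongest defence is that this is a legitimate study of how lean and high-fat men respond. The protocol says openly, twice, that everyone is treated, and it never presents the control group as untreated. The objective refers to people with excess adipose tissue, which fits a before-after study in high-fat men with a lean reference group. All of that stands: the protocol does not contradict itself about who is treated. But the objective as worded asks for the effect of the treatments, and a reference group for adiposity does not provide it.

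There are also safeguards. Diet is to stay unchanged; smokers, men on weight-reducing diets and users of anti-inflammatory drugs are excluded; draws are in the morning and fasting. These limit some background variation, but not season, assay drift or the activity restriction.

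The last week has no sessions, and together with the draws after sessions 10 and 20 it gives some information on sequence. It would be too strong to say that no period is untreated. That week follows 20 treatments, however, so carry-over is possible and it is not a clean control interval.

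The drift sizes are assumed. The same percentages would apply to any before-after study of 15 people, and they say nothing about how large the drift is here.

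Several stronger readings are tempting and not supported:

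- A reader might infer that changes will be reported as treatment effects. The protocol contains no reporting rule, so this is only a risk.
- A reader might infer that the two groups are treated in different seasons. The protocol does not say so; it is silent on timing.
- A reader might object that different starting levels distort comparisons on the raw scale. The choice of scale is commonly left to the analysis plan, which is not at hand.
- A reader might take stages 8 and 9 of the Research plan as a spare fifth draw that could become a second baseline. Those stages are identical, and both the Research plan and Blood collection count four, so a listing error is the likely explanation.

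**Conclusion.** The point holds as a mismatch between objective and design. As designed, the trial can describe the before-after change in each group and whether that change differs by body-fat group. It cannot isolate the effect of 20 cryostimulation treatments, and no analysis plan could repair that, because the missing comparison is not in the data.

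This conclusion rests only on the protocol's statements that both groups receive all sessions and on the absence of any untreated comparison. It does not depend on the drift figures. Those show how far a before-after test can mislead: from about 11% false positives at an assumed drift of 0.2 SD to about 77% at 0.75 SD with 15 men, with the actual drift unknown.

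It should be corrected before the trial is reported against its present objective, since the correction changes what may be concluded. It does not follow that the study is without value.

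**What to change.** 1. In Research Methodology, rename the control group as a treated comparison group with normal body fat.
2. In the Research Project objective, restate the aim as (a) the before-after change in men with more than 25% body fat and (b) the difference in change between the two body-fat groups. Add that neither is a treatment-versus-no-treatment effect.
3. State that both groups are run in the same calendar weeks where feasible, so that season does not differ between them. This does not remove season from the before-after change itself.

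Items 1 and 2 cost only wording. Item 3 costs some scheduling. No extra participants or samples are needed. The downside is a weaker claim: the trial would no longer offer a causal estimate of the treatment effect.

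Keeping the present objective would instead need an untreated or delayed-start comparison among high-fat men, which is a different and larger study. For scale, 15 against 15 would have about 59% power for a difference of 0.8 SD (assumed), and 80% power would need about 25 per group (normal approximation, two-sided 5%). An extra pre-treatment sample is not part of this fix. It would be a real additional draw, and deleting the duplicated stage would not pay for it.

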**Blood collection**

In all participants, according to valid provisions of law, laboratory diagnostician will collect venous blood 4 times, in the morning, in fasting conditions: before commencement of whole body cryostimulation, after 10^th^ and 20^th^ sessions of whole body cryotherapy and a week after the end of the experiment.

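### Read literally, the request for no physical activity is a second change running alongside cryostimulation, and the design cannot separate the two

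*Protocol*

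**What the plan says.** Research Methodology gives both lifestyle rules in one sentence: "Participants will be asked not to change their nutritional habits and not to take any physical activity during the whole experiment". The first rule keeps a habit constant. The second, on its plain reading, removes one.

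The same section says "All participants will be subjected to whole body cryostimulation". The two groups are formed by body fat, "normal (<23%) or increased (>25%) percentage of adipose tissue determined for age and sex", and not by treatment. The only lifestyle assessment described is the dietary interview.

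The Research Project objective is to evaluate 20 treatments for their effect on adipocytokines, with "reduction of inflammation in people with excessive adipose tissue and improve lipid metabolism". Under Blood collection, samples are taken "before commencement of whole body cryostimulation, after 10^th^ and 20^th^ sessions of whole body cryotherapy and a week after the end of the experiment". The Research plan lists medical examination, nutritional interview and anthropometry before the first draw. It gives no intervals between them and no period under the activity rule.

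**The concern.** The objective attributes changes from baseline to cryostimulation. With no group left untreated, that attribution depends on nothing else relevant changing over the same weeks. The diet rule serves that purpose. The activity rule, taken literally, works against it, because an active man would start cryostimulation and stop exercising within the same observation window.

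If stopping activity moves lipids, adipokines or inflammation markers, the before-after change is the sum of two effects. Nothing that the Protocol collects would allow them to be separated. The Protocol does not say that activity affects these markers. However, asking participants to control diet and activity makes sense only if both could influence the results.

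An analysis plan could not repair this later. It cannot adjust for activity that was never recorded, and it cannot supply men who had the restriction without cryostimulation.

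**Working it through.** The Protocol gives no sample-size, power or significance figure on this point, so there is nothing to reproduce. The check has two parts.

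**1. What the text fixes and leaves open**

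| Item | Diet | Physical activity |
|---|---|---|
| Instruction | Keep the habit | None, if read literally |
| Assessed before the first draw | Yes, by interview | Not described |
| Recorded during the study | Not described | Not described |
| Start relative to the baseline draw | No issue if the habit is unchanged | Not stated |
| Group with the rule but no cryostimulation | None | None |

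- Exposure: "20 sessions of whole body cryostimulation (1 treatment per day, from Monday to Friday, except on holidays" gives 20 / 5 = 4 weeks at least, longer if holidays fall within it. The last draw is one week later, at about 5 weeks.
- End of the rule: it applies during the experiment, while the last draw is placed a week after the experiment ends. Literally, that draw may fall outside the restriction, so the four samples need not share one activity condition.

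**2. How much an unseparated shift could matter (illustration)**

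Inputs from the Protocol:
- "30 men aged 20-25 will be qualified to participate in the research".
- The control group has 15 men, which leaves 30 - 15 = 15 in the higher-fat group.

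Assumptions, none of them in the Protocol:
- cryostimulation effect of zero;
- two-sided 5% level;
- t-tests on change from baseline to one later draw;
- a shift d due to stopping activity, in units of the SD of change.

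Before-after test in one group: df = 14, critical t = 2.145, noncentrality = d × √15 = 3.873d.

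Difference in change between groups: df = 28, critical t = 2.048, noncentrality = d × √(15/2) = 2.739d. Here d is the difference between the groups' shifts.

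In both cases P(reject) = P(|T| > critical t), with T noncentral t.

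| d (assumed) | Noncentrality, before-after | P(false result), n = 15 | Noncentrality, between groups | P(false result), 15 vs 15 |
|---|---|---|---|---|
| 0.1 | 0.387 | 0.07 | 0.274 | 0.06 |
| 0.2 | 0.775 | 0.11 | 0.548 | 0.08 |
| 0.3 | 1.162 | 0.19 | 0.822 | 0.12 |
| 0.5 | 1.936 | 0.44 | 1.369 | 0.26 |

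At 0.1 SD the inflation over 0.05 is small, and at 0.5 SD it is large. The before-after column needs no difference between the groups, only an average shift within one. The documents do not show where in this range, if anywhere, the true shift lies.

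**The case against.** The strongest objection concerns the wording. Participants are asked, not ordered, and the English is plainly not native. The phrase may mean only that no new activity be taken up, which is close to the diet rule and would leave no co-intervention. This stands as a limit on confidence. It does not remove the point, because the two readings give different studies and the text does not say which is meant.

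Second, the start date is not given. A reader might infer that the restriction begins with the first session, but the documents do not say so. It could begin earlier, since several procedures precede the first draw. What can be said is that the start is undated and no run-in is described.

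Third, a reader might infer that leaner men were more active, that the ban therefore hits the control group harder, and that a worsening there would pass for a benefit in the higher-fat men. The documents do not support this. Groups are defined by body fat alone and habitual activity is neither reported nor measured. The existence, direction and size of any group difference are unknown. Moreover, if only the lean men were affected, the before-after result in the higher-fat men would not be biased by the ban.

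Fourth, holding everyone at a common activity level is a recognised way to reduce variation during a study, and other time-related influences would remain unseparated without an untreated group. Both are true. However, a common level helps only if it is in place before baseline, and the general limitation is no reason to add an avoidable change to it.

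**Conclusion.** The point holds in a limited form. On its literal reading, the activity instruction is a possible co-intervention over at least 4 weeks, and its effect could not be separated from that of cryostimulation in the before-after comparison. No run-in, activity record or untreated group is described that would allow it. A differential effect between the body-fat groups cannot be ruled out or checked, and no direction of bias should be claimed.

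If stopping activity shifted a marker by 0.1 to 0.5 SD of change and cryostimulation did nothing, the chance of a false before-after finding in 15 men would be 0.07 to 0.44. A group difference of the same size would give 0.06 to 0.26. The shifts, the tests and the 5% level are assumptions, and that activity affects these markers is plausible but not stated in the Protocol. Confidence is moderate because of the ambiguous wording. The correction should be made before enrolment, since unrecorded activity cannot be recovered afterwards.

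**What to change.** Reword the activity instruction in Research Methodology to match the diet rule: participants keep their habitual physical activity unchanged, with no new training, from before the first blood draw until the last. This settles both readings of the present sentence.

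Ask about habitual activity at the nutritional interview, and about current activity at each of the four blood draws, so that departures can be described and a group difference examined.

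If abstention is really intended, say so and state its start and end dates. Begin it well before the baseline sample and continue it through the last draw, so that all four samples are taken under the same condition. Activity should still be recorded.

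The cost is one sentence and a few questions at visits already planned. Allowing habitual activity may add slightly to within-man variability. The change does not supply an untreated group, so other influences over time remain unseparated.
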